### Sample size

2.4

This study is a randomized controlled trial with two groups: the mobile health intervention group and the conventional education group. The primary outcome is the health behavior formation rate among the participants. Based on a literature review (48), the compliance rate for behavior formation in the mobile health intervention group is expected to be 90%, compared to 60% in the control group. The significance level is set at *α* = 0.05, with a 90% confidence level. Using PASS15 software, the sample size for the intervention group was calculated as N1 = 23, and for the control group, N2 = 23. Considering a 20% follow-up loss rate, at least 29 participants are required in each group, resulting in a total of 58 participants.

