##### Proportion of individuals adopting health behaviors

2.8.1.1

The health behavior was assessed using a self-designed health behavior scale, which consists of five domains: (1) frequency of personal protective measures during contact with livestock (5 items), (2) frequency of personal protective measures when handling lambs and aborted materials (5 items), (3) frequency of personal protective measures when vaccinating livestock (5 items), (4) frequency of cleaning measures when cleaning animal pens (3 items), and (5) frequency of hand hygiene maintenance after contact with cattle, sheep, their placental tissues, or meat products (4 items). Each item was rated on a 5-point Likert scale: “Never (0),” “Rarely (1),” “Sometimes (2),” “Often (3),” and “Almost Always (4).” One reverse-scored item was included in each domain. The total score ranges from 0 to 110, with higher scores indicating better health behavior.

This scale was developed to evaluate the frequency of health behaviors related to occupational safety and hygiene practices among individuals at risk for brucellosis.

The proportion of individuals adopting health behaviors is calculated by determining the proportion of participants who meet the health behavior standard, as assessed by the health behavior questionnaire. A threshold score will be established to determine whether an individual has adopted health behaviors, with a score above 70 considered indicative of good health behavior formation. The adopting proportion is then calculated by dividing the number of individuals exceeding this threshold by the total number of participants.

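### The behaviour primary outcome cuts a 22-item score at an unexplained 70, at a cost of up to about half the effective sample size, and the planned score analysis is unranked and not baseline-adjusted

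*Protocol article*

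**What the plan says.** Section 2.8.1 names two primary outcomes, and the first is the proportion of participants who have adopted health behaviours. Section 2.8.1.1 builds it from a self-designed scale with five domains of 5, 5, 5, 3 and 4 items, each scored 0 to 4, and states a total range of 0 to 110. The total is then cut: "A threshold score will be established to determine whether an individual has adopted health behaviors". The same sentence goes on to supply the value: "with a score above 70 considered indicative of good health behavior formation". No rationale or validation for 70 is given.

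Section 2.4 sizes the trial on this binary outcome: "The primary outcome is the health behavior formation rate among the participants". The rate in the intervention group "is expected to be 90%, compared to 60% in the control group". The result is 23 per arm, raised to 29 per arm (58 in total) for 20% loss.

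Section 2.1 and Table 1 schedule the questionnaire at months 0, 3, 6, 9 and 12. Section 2.9 plans a t-test or Mann-Whitney comparison between arms of the change in scale scores from baseline to endpoint, and linear and logistic regression on the multiply imputed data. Tests are two-sided at 5%. It does not single out the behaviour score, rank it against the proportion, or say that the baseline score enters the regression.

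**The concern.** Cutting a score treats a patient at 71 like one at 88, and a patient at 69 like one at 20. In a trial of 58 patients that loss is expensive, and here it buys no saving in data collection because the full score is already available at every visit.

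The analysis that would recover the information is only half in place. The planned change-score test has no stated standing for the behaviour outcome. If the proportion just misses significance while the score shows a clear difference, the plan does not say how much weight the score carries. The test is also on unadjusted change, which wastes part of the value of having measured baseline.

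Finally, the cut sits on a scale whose stated range does not match its items, so it is unclear how demanding a standard 70 is.

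**Working it through.** **Inputs from the protocol article.** Rates 0.90 and 0.60, 23 per arm evaluable, 29 per arm randomised (section 2.4); two-sided 5% (section 2.9); 22 items scored 0-4 and a cut above 70 (section 2.8.1.1).

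**Assumed, because the document gives no figure.** Score roughly normal with equal SDs and a pure shift between arms; SD 8 to 25 where the ceiling matters; correlation between baseline and follow-up of 0.3 or 0.5.

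**1. The plan's own sample size.** The normal-approximation formula with pooled variance under the null is n = [1.96·√(2·0.75·0.25) + z_power·√(0.09 + 0.24)]² / 0.30². It gives 32 per arm for 80% power and 42 for 90%. The stated 23 is not reproduced at two-sided 5% with either. Section 2.4 gives "with a 90% confidence level" and no figure labelled as power. The dropout step does reproduce: 23/0.8 = 28.75, so 29.

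**2. Power of the proportion.** Sum Bin(a; n, 0.90)·Bin(b; n, 0.60) over all outcomes (a, b) that the test rejects:

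| per arm | chi-square | Fisher |
|---|---|---|
| 23 | 68.9% | 57.5% |
| 29 | 77.8% | 68.1% |

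**3. The same effect on the score scale.** For a common cut, the shift in SD units is Φ⁻¹(0.90) − Φ⁻¹(0.60) = 1.282 − 0.253 = 1.028. A two-sample t-test at this shift has 92.6% power at 23 per arm and 97.0% at 29. For 80% power, n = 2(1.96 + 0.842)²/1.028² = 14.8, so 15 per arm against 32 for the proportion. The cut therefore costs 1 − 15/32 = 53% of the sample in this case. In power terms, 68.9/92.6 = 74% is kept at 23 per arm.

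**4. Ceiling.** 22 items × 4 = 88, not 110, so 70 is 64% of the stated maximum but 80% of the attainable one. With 90% of the intervention arm above 70, its latent mean is 70 + 1.282·SD, which reaches 88 when the SD is 18/1.282 = 14. Simulating normal scores clipped at 88 with 90% v 60% held fixed, t-test power at 23 per arm falls from about 92% (SD 8) to about 82% (SD 25), and Mann-Whitney from about 91% to 85%. Even at SD 25, with over 70% of the intervention arm at the maximum, the score beats the chi-square comparison by about 13 points. In that case 23 per arm already gives over 80% power against 32 for the proportion, so the cost of the cut is nearer a quarter to a third of the sample.

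**5. Change score against baseline adjustment.** In units of the score SD, change has SD √(2(1 − ρ)) and the baseline-adjusted residual has SD √(1 − ρ²). At 23 per arm and a shift of 1.028, with no ceiling:

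| ρ (assumed) | change SD | power | adjusted SD | power |
|---|---|---|---|---|
| 0.3 | 1.183 | 82% | 0.954 | 95% |
| 0.5 | 1.000 | 93% | 0.866 | 98% |

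**The case against.** Several stronger readings are tempting, and the document does not support them.

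- *A reader might infer that the cut discards most of the power.* It does not: about three quarters of the power is kept by chi-square, and just over 60% if Fisher is set against the t-test (57.5/92.6).
- *A reader might infer that the full score goes unanalysed.* Section 2.9 plans a between-arm comparison of change in scale scores, and the behaviour instrument is naturally covered by that. At a correlation of 0.5 this test alone has 93% power. What is left is its rank and its efficiency.
- *A reader might infer that the cut-off is still open.* The future-tense wording and the value 70 stand in one sentence, and the ordinary reading is that 70 is the threshold. It is stated but not explained.
- *A reader might blame the low power wholly on dichotomising.* Part of it is the 23 per arm, which does not follow from the stated inputs. A trial sized at 32 or 42 per arm would be adequately powered on the proportion.

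A further objection has real weight. The proportion reaching a behaviour standard is a legitimate target, the trial is sized on it, and a mean difference on a self-designed scale answers a different question. Replacing the primary outcome would change the estimand and the basis for sizing, so that is not proposed. It is also true that ranking supportive analyses is often left to an analysis plan, and one is said to exist. But the unadjusted change-score comparison, the unexplained cut and the inconsistent range are all in the text as it stands.

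**Conclusion.** The point holds in a limited form. The behaviour primary outcome is a dichotomised score with an unexplained cut, and under the trial's own rates it is below 80% power even with no dropout (78% by chi-square, 68% by Fisher at 29 per arm). At 23 per arm the full score would raise power from 69% to about 93%, or to about 82-92% with a ceiling at 88. The cut thus costs up to about half the effective sample size, and less if many patients sit at the maximum.

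The planned score analysis softens this but has no stated rank for behaviour. Its unadjusted form gives up about 13 points of power at a correlation of 0.3 and about 5 at 0.5. The score figures rest on assumed normality, equal SDs, a pure shift and the assumed correlations; only the figures for the proportion rest on the document's inputs alone. The mismatch between 0-110 and 0-88 is arithmetic and needs no assumption.

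**What to change.** 1. Keep the proportion above the cut-off as the primary responder outcome, and adjust its comparison between arms for baseline score.
2. Name as the key supportive analysis a linear regression of the total behaviour score at one stated time point on arm and baseline score, within the planned multiple imputation. It takes the place of the unadjusted change-score test for this outcome.
3. Before any outcome data are seen, reconcile the stated 0-110 range with the 0-88 that 22 items scored 0-4 allow, confirm the cut-off on the corrected scale, and give the reason for it.

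Cost: wording only. The data are already scheduled, and linear and logistic regression are already in section 2.9. A mean difference is harder to read than a rate, which is why the rate stays as the primary outcome, and a ceiling in the score would shrink the gain. The change does not repair the sample size calculation, which needs its own correction.

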### Study design

2.1

The study is an intervention randomized controlled trial in Baoding No. 4 Central Hospital, Hebei Province. The study employs quantitative research methods, using questionnaires based on brucellosis-related knowledge and internationally recognized scales for measurement. This approach ensures the objectivity of the study. The study will be conducted from December 2024 to December 2025. The intervention will last for 3 months, followed by a 12-month follow-up phase for data collection and evaluation. The questionnaire was given at the beginning then every 3 months which was then analyzed. The control group will receive conventional education, while the experimental group will receive mHealth education. The study aims to compare the effectiveness of mHealth interventions on the health behaviors of brucellosis patients based on the HAPA model, hypothesizing that mHealth interventions are more effective than conventional interventions (43). The flow chart of the study is shown in Figure 2 and Table 1.

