**Figure 2 fig2:**
[figure not shown]
Flow chart of patient recruitment and study implement.

**Table 1 tab1:** Timeline for study enrollment, intervention, and evaluation.

	Study period						
	Recruitment	Allocation	Intervention		Follow-up		
Timepoint	-T1	0	Month 0	Month 3	Month 6	Month 9	Month 12
Enrollment							
Informed consent	√						
Eligibility screen	√						
Allocation		√					
Intervention							
HAPA-mHealth							
Control							
Assessments							
Sociodemographic variables			√				
Proportion of individuals adopting health behaviors			√	√	√	√	√
Knowing rate of health knowledge			√	√	√	√	√
Refill and medication adherence scales			√	√	√	√	√
Quality of life			√	√	√	√	√
Depression and anxiety			√	√	√	√	√
Perceived stress scale			√	√	√	√	√
Perceived social support			√	√	√	√	√
Satisfaction				√	√	√	√

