##### Pre-intentional stage

2.5.1.1

At this stage, patients have not yet developed a willingness to improve health behaviors or engage in functional exercises.

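### The primary outcome is called behaviour formation but counts everyone scoring above 70 at a visit, including patients already above 70 at Month 0

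*Protocol article*

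**What the plan says.** The Abstract lists health behaviour formation as a primary outcome. Section 2.4 (Sample size) says "The primary outcome is the health behavior formation rate among the participants" and sizes the trial on this expectation: "the compliance rate for behavior formation in the mobile health intervention group is expected to be 90%, compared to 60% in the control group".

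Section 2.8.1.1 gives the derivation. The cut is stated as "with a score above 70 considered indicative of good health behavior formation", and the proportion follows: "The adopting proportion is then calculated by dividing the number of individuals exceeding this threshold by the total number of participants". Cut, numerator and denominator are all fixed, and none refers to Month 0.

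Section 2.1 says of the assessments: "The questionnaire was given at the beginning then every 3 months". The Table 1 row "Proportion of individuals adopting health behaviors" is ticked at Months 0, 3, 6, 9 and 12. Neither the inclusion criteria (2.3.1) nor the exclusion criteria (2.3.2) mention the behaviour score.

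Section 2.9 uses baseline values for changes in scale scores and as auxiliary variables for imputation. It states no use of the Month 0 score in comparing the arms on the proportion above 70.

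**The concern.** Formation implies a change from not having a behaviour to having it. The rule in 2.8.1.1 measures a state at one visit. The Month 0 tick in Table 1 shows that the rule can be met before any intervention has been given.

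Two things are at stake. First, interpretation: a rate reported as formation would mix patients who changed with patients who were already there, in both arms, and a reader could not separate them. Second, precision: the Month 0 score is likely to predict the later score and is already collected, yet the comparison that matters most is not said to use it. The link between the sample size assumption and the outcome as derived is also left open.

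**Working it through.** **1. The rule applied literally** (hypothetical patients, cut at 70)

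| Month 0 | Endpoint | What happened | Result under 2.8.1.1 |
|---|---|---|---|
| 75 | 75 | no change | formed |
| 80 | 72 | worsened | formed |
| 35 | 69 | rose 34 points | not formed |

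**2. The plan's own sample size.** Inputs from 2.4: 90% v 60%, α = 0.05, 23 per arm, 20% loss. With unpooled variance, n = (z_α + z_power)² × (0.9×0.1 + 0.6×0.4) / 0.3². One-sided 0.05 and an assumed 80% power give (1.645 + 0.842)² × 0.33 / 0.09 = 22.7, so 23. Then 23 / 0.8 = 28.75, so 29 per arm. The two-sided 0.05 of 2.9 would give 29 evaluable per arm at 80% power. That gap is a separate matter. It is why the powers below start at 69%, and it does not come from the 70-point rule.

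**3. What existing adopters would do to the rates, if 60% and 90% are formation rates.** Let b be the share above 70 at Month 0. The article does not give b, so a range is assumed, equal in both arms. Assume also that all who start above 70 stay there. The status rate is then b + (1 − b) × formation rate. Power is by exact enumeration of the Pearson chi-square test, two-sided 0.05, 23 per arm.

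| b | Intervention | Control | Difference | Power |
|---|---|---|---|---|
| 0% | 90% | 60% | 30 points | 69% |
| 20% | 92% | 68% | 24 points | 56% |
| 30% | 93% | 72% | 21 points | 50% |
| 40% | 94% | 76% | 18 points | 42% |

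**4. The other reading: 60% and 90% are already status rates.** Then no power is lost to this rule, but they are not formation rates. The implied rate among those not yet above 70 is (status − b) / (1 − b). At b = 20% this is 0.7/0.8 = 87.5% v 0.4/0.8 = 50%. At b = 40% it is 0.5/0.6 = 83% v 0.2/0.6 = 33%.

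**5. What the rule reports when nobody truly changes.** Assume bivariate normal scores, 40% above the cut at both times, and test-retest correlation of 0.6, 0.8 or 0.9. The reported rate is 40% in each case. Of this, about 26, 30 and 33 points are patients above the cut both times, and about 14, 10 and 7 points cross it by measurement noise.

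**6. Would restricting to those at or below 70 at Month 0 be better as the primary analysis?** With 23 evaluable per arm and b = 20%, 30% and 40%, about 18, 16 and 14 per arm remain. Exact power for 90% v 60% is then 56%, 55% and 47%, a gain of 0 to 5 points over step 3. Under step 5, the noise crossings as a share of the 60% at risk are 14.3/60 = 24%, 9.9/60 = 17% and 6.9/60 = 12%. The restricted rate therefore carries a false component of its own.

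**The case against.** The strongest reply is that the outcome is named and defined as a status almost everywhere. Sections 2.8.1 and 2.8.1.1 and Table 1 speak of the proportion adopting health behaviours, and 2.8.1.1 gives formation an operational meaning. Comparing a status at follow-up between randomised arms, with everyone in the denominator, is a standard intention-to-treat endpoint. Existing adopters balance in expectation. The programme also aims at maintenance, so patients already above 70 are relevant to it. Section 2.9 compares changes in scale scores, the Discussion promises longitudinal analysis, and a fuller analysis plan may adjust for baseline.

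Most of this stands. It defeats three stronger readings that a reader might infer:

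- **That the rule biases the comparison.** It does not. With 29 per arm a chance imbalance at Month 0 could matter, but that is a question of precision.
- **That the trial is underpowered because of this rule.** Section 2.4 takes its rates from a cited source that is not shown, and its wording fits either meaning. The share above 70 at Month 0 is nowhere given, and the assumption that existing adopters all stay above the cut is generous: in step 5, 17% to 36% of them fall below it by noise alone.
- **That the trial presumes every enrolled patient starts without the behaviour.** The phrase "patients have not yet developed a willingness to improve health behaviors" in 2.5.1.1 describes one stage of the behavioural model. It does not describe the enrolled population.

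The reply does not remove the mismatch in the stated text. The Abstract and 2.4 call the outcome formation, 2.8.1.1 uses that word for the cut, and the rule there needs no change in the patient. An unseen analysis plan could add adjustment, but it would not alter the rule and label fixed here.

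**Conclusion.** The point holds as a mislabelled primary outcome together with a collected Month 0 score that has no stated role in the comparison. The randomised comparison of the proportion above 70 is sound and should remain primary. The rate in either arm cannot be reported as formation, because it includes patients who were already above 70 and may be unchanged or worse.

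The size is conditional. If 60% and 90% apply only to patients not yet above 70, and 20% to 40% are already above and stay there, the expected difference falls from 30 points to 24 to 18, and power at 23 per arm from 69% to 56% to 42%. If the two figures are already proportions above 70, this rule costs no power and only the label is wrong. The documents do not settle which applies. The literal examples in step 1 need no assumption.

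**What to change.** - **Sections 2.4 and 2.8.1.1, and the Abstract:** name the primary outcome the proportion scoring above 70 at the endpoint visit, on all randomised participants.
- **Section 2.9:** compare the arms on it with a logistic regression adjusted for the Month 0 score. Table 1 places allocation before the Month 0 column, so state that the Month 0 questionnaire is completed before the envelope is opened.
- **Supportive table, by arm:** the share newly above 70 among those at or below 70 at Month 0, and the shares maintained and lost among those above 70 at Month 0. Limit any claim of formation to the new-adopter figure. Treat it as supportive, since it rests on fewer patients and includes noise crossings of the cut.
- **Section 2.4:** state whether the 60% and 90% are proportions above 70 or rates of new adoption.

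The cost is wording, one model term and one extra table from data already scheduled, with no new visits or patients. The new-adopter rate will have a wider interval than the all-randomised figure. Making it the primary outcome would need more patients: to keep 23 evaluable per arm after 20% loss, 37 randomised per arm at b = 20% (23/0.8 = 28.75, so 29; 29/0.8 = 36.25, so 37), against the planned 29.

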##### Knowing rate of health knowledge

2.8.1.2

The Brucellosis Health Knowledge Awareness questionnaire was designed based on the “National Brucellosis Surveillance Program” and tailored to the specific context of Baoding City, Hebei Province. The questionnaire includes items on awareness of brucellosis, its clinical symptoms, and modes of transmission. Participants indicated their knowledge, with correct answers marked as “aware” and incorrect or unknown answers as “unaware.”

The awareness rate for each item was calculated as the number of correct responses divided by the total number of valid respondents, multiplied by 100%. The overall knowledge awareness rate was calculated by dividing the total number of correct responses by the product of the total number of respondents and the total number of questions, then multiplying by 100%.

This questionnaire assesses health knowledge about brucellosis within the local population, providing essential information for health interventions.

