#### Primary outcome

2.8.1

The primary outcome is the proportion of individuals adopting health behaviors and knowing rate of health knowledge.

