### Statistical analysis

2.9

Statistical analyses will be performed using SPSS Statistics 26.0 software. Count data will be expressed as the number of cases and rate (%), while measurement data will be presented as mean ± standard deviation. Before performing parametric tests, normality assumptions will be tested using the Shapiro–Wilk test. If data is normally distributed, parametric tests, such as the independent *t*-test, may be used. However, if the normality assumption is violated, non-parametric tests, such as the Mann–Whitney U test, will be used to compare changes in scale scores between baseline and endpoint between the two groups. The Wilcoxon signed-rank test will be employed for within-group comparisons of scale scores between baseline and endpoint. Demographic and clinical characteristics at baseline will be summarized descriptively for each group. Categorical variables will be reported as counts and percentages, and continuous variables as mean ± standard deviation.

For the primary analysis, all randomized participants will be included in an intention-to-treat (ITT) analysis, regardless of whether they complete the intervention. For secondary analyses, only participants who complete the intervention and follow-up will be included in a per-protocol (PP) analysis.

Regarding missing data, we will explore the missing data and compare the distribution of key variables. If the missing data is reasonable in amount and assumed to be Missing at Random (MAR), multiple imputation methods will be used to handle the missing data for both ITT and PP analyses. This ensures that the handling of missing data is consistent across both analysis groups. Baseline variables will be used as auxiliary variables for imputation, and multiple imputed datasets will be generated. Linear regression and logistic regression will be applied to analyze the imputed datasets, and the results will be pooled to provide final estimates and standard errors. A two-sided test will be used, and statistical significance will be defined as *p* < 0.05. The detailed statistical analysis plan for this study is available for public access at the Chinese Clinical Trial Registry: ChiCTR Statistical Analysis Plan (https://www.chictr.org.cn/showproj.html?proj=196659).

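### The knowledge primary outcome is defined only through group-level rates, with no value per participant, so it does not fit the planned intention-to-treat, imputation and regression analyses

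*Protocol article*

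**What the plan says.** Section 2.8.1 of the protocol article gives knowledge primary status: "The primary outcome is the proportion of individuals adopting health behaviors and knowing rate of health knowledge".

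Section 2.8.1.2 describes the instrument by its topics, without a number of questions: "The questionnaire includes items on awareness of brucellosis, its clinical symptoms, and modes of transmission". Each answer is coded as aware or unaware. Two rates follow:

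- Per item: "The awareness rate for each item was calculated as the number of correct responses divided by the total number of valid respondents".
- Overall: "dividing the total number of correct responses by the product of the total number of respondents and the total number of questions".

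Section 2.9 has four sentences that bear on how such an outcome would be handled:

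- On counts: "Count data will be expressed as the number of cases and rate", with a percentage.
- On the named between-arm tests, the t-test or, if normality fails, the Mann–Whitney test: the latter "will be used to compare changes in scale scores between baseline and endpoint between the two groups".
- On missing data: multiple imputation with baseline variables as auxiliaries, after which "Linear regression and logistic regression will be applied to analyze the imputed datasets".
- On the analysis set: the primary analysis is intention-to-treat and covers everyone randomized.

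Table 1 schedules the knowledge measure at month 0 and at months 3, 6, 9 and 12.

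**The concern.** Section 2.9 is built on participants: all who were randomized are analysed, missing values are imputed from their baseline variables, and regression models are fitted to the completed data. Section 2.8.1.2 supplies nothing at that level. Its overall rate is a single figure for a group at a visit, with answers rather than people in the denominator. Its item rates are single figures for a group and a question.

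Two things are at stake. First, a primary outcome with no participant value leaves the analyst to invent one after the data are in, including the treatment of unanswered questions. Second, because each answer is binary and logistic regression is among the named models, an analyst could take the individual answer as the unit. Answers from one person are correlated, so treating them as independent would make the standard error too small.

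**Working it through.** **1. Is the missing participant value peculiar to this outcome?**

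| Outcome | Section | Value for one participant |
|---|---|---|
| Health behaviour (primary) | 2.8.1.1 | Total score; standard met if above 70 |
| Medication adherence | 2.8.2.1 | Score 7–28 |
| EQ-5D-5L visual analogue | 2.8.2.2 | Score 0–100 |
| PHQ-4 | 2.8.2.3 | Score 4–16 |
| PSS-4 | 2.8.2.4 | Summed score |
| Social support | 2.8.2.5 | Score 12–84 |
| CSQ-3 | 2.8.2.6 | Total score |
| Knowledge (primary) | 2.8.1.2 | None given |

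Knowledge is the only outcome in the list without one.

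**2. Do the two denominators agree?** Let n be the respondents, K the questions, c_j the correct answers to item j, and v_j the valid respondents to item j.

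- Item rate = c_j / v_j ("divided by the total number of valid respondents").
- Overall rate = Σc_j / (nK), which is the average over items of c_j / n.

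The overall rate equals the average of the item rates for certain only if v_j = n for every item. If v_j < n, a respondent without a valid answer is left out of the item rate but stays in the overall denominator, in effect as not correct.

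**3. How does the pooled rate relate to a participant score?** Let x_i be participant i's number correct. Then Σx_i / (nK) = (1/n) Σ(x_i / K). When every item is answered, the pooled rate is exactly the mean of the individual percentages. The choice of unit then leaves the unadjusted difference between arms unchanged and affects only its standard error and p-value.

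**4. What would happen if answers were tested as independent?** The plan gives no figure for this outcome to reproduce; its sample size (23 per arm, 29 after loss) rests on the behaviour outcome. Inputs:

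- Two-sided α = 0.05 (sections 2.4 and 2.9).
- K and the within-person correlation ρ: not stated. Assumed K = 5, 10, 20 and ρ = 0 to 0.3.

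Formulas: design effect DE = 1 + (K − 1)ρ; true error = 2[1 − Φ(1.96 / √DE)].

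Worked ends of the range:

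- K = 5, ρ = 0.05: DE = 1 + 4 × 0.05 = 1.2, true error 7.4%.
- K = 20, ρ = 0.3: DE = 1 + 19 × 0.3 = 6.7, true error 44.9%.

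| K | ρ = 0 | 0.05 | 0.1 | 0.2 | 0.3 |
|---|---|---|---|---|---|
| 5 | 5.0% | 7.4% | 9.8% | 14.4% | 18.6% |
| 10 | 5.0% | 10.4% | 15.5% | 24.2% | 30.8% |
| 20 | 5.0% | 16.1% | 25.0% | 37.1% | 44.9% |

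**5. Check by simulation.** Beta-binomial answers were generated with no true difference (assumed 60% correct, 23 and 29 per arm, 20,000 runs per cell). The pooled-answer test agreed with the table within about one percentage point; for example, K = 20 and ρ = 0.3 gave 45.0% with 23 per arm and 44.7% with 29. A t-test on each participant's number correct gave 4.7% to 5.5% in every cell.

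**The case against.** The strongest reply is that no invalid test is planned. A reader might infer that, because rates are count data, the arms will be compared on all answers as if independent, and that the p-value for this outcome is therefore already invalid. The document does not support that. Its sentence on counts is a rule for reporting, and no chi-square or similar test is named for any outcome. Section 2.9 otherwise points towards participants, and linear regression on each person's percentage correct would fit it well. The raw data for such a score exist, since every answer is coded. Section 2.9 also refers to a separate statistical analysis plan, not shown, where the test and unit could properly be set out.

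It is also fair to say that the pooled rate is not the only definition, because item rates are given too. Those take one answer per person, so clustering within a person does not arise for them. The article does not say that items can be left unanswered on the online form, and it already scores unknown answers as unaware.

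All of this stands against a claim of a planned error. It does not remove the point about the definition. The article does more than leave the outcome to another document: it states formulas for it, those formulas yield no participant value, and their denominators differ as written.

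**Conclusion.** The point holds as a defect in how a primary outcome is defined. Section 2.8.1.2 gives group-level rates only, which do not match the participant-level analyses in section 2.9, and it divides by valid respondents in one place and by all respondents times all questions in the other. These are facts of the text and need no assumption; the denominators matter in practice only if items go unanswered.

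The inflated false-positive rate is a conditional risk. It arises only if total correct answers are compared as independent counts, and its size, about 7% to 45%, depends on assumed item numbers (5 to 20) and within-person correlations (0.05 to 0.3). With no within-person correlation there is no inflation, and with a participant-level analysis the error stays near 5%. The definition should be corrected, but the figures should not be read as the error rate of the trial's stated analysis.

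**What to change.** - In section 2.8.1.2, define the outcome as each participant's percentage of questions answered correctly (0 to 100), and state one rule for unanswered items that applies to the participant score, the item rates and the overall rate.
- In section 2.9, compare arms on this percentage by linear regression on arm and baseline score, within the multiple imputation already planned. Table 1 already collects the baseline score at month 0.
- Report the pooled and per-item rates descriptively only.

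The cost is a few sentences in the protocol and, if needed, the statistical analysis plan. No new data or participants are required. When all items are answered, the unadjusted difference between arms is the same as with the pooled rate; adjusting for baseline may move the estimate slightly.
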